## Methods: participants, interventions and outcomes

### Study setting

The trial will be conducted at five German medical centers with high expertise in shoulder surgery. All investigators are shoulder surgeons certified by the German, Austrian, and Swiss Society for Shoulder and Elbow Surgery (DVSE) and renowned experts in the field. In preparation of the trial, participating centers had to provide the average number of potentially eligible patients using hospital data management systems and ICD-10 codes of the included pathologies (M75.2, M75.6, S43.4, S46.1, S46.2) over the past 5 years to ensure access to the relevant target population and site capability. Capability of recruitment and recruitment progress by predefined milestones will be independently monitored by a CRO for all centers. All investigators and observers at each study site were trained in ICH-GCP E6 (R2) guidelines prior to study initiation.

The following centers met the selection criteria and have agreed to participate in the conduct of the trial: Department of Trauma Surgery, University Hospital Regensburg; Center for Musculoskeletal Surgery, Charité Berlin; Department of Shoulder Surgery, Vivantes Auguste-Viktoria-Clinic Berlin; Department of Trauma Surgery, Hand Surgery and Sports Medicine, St. Vincentius Clinic Karlsruhe; Sporthopeadicum Regensburg/Straubing.

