#### Trial flow

One hundred ninety-two patients (*n* = 96 for experimental group, *n* = 96 for standard-of-care group) with LHB tendon disorders meeting all eligibility criteria will be randomized equally to implant-free loop tenodesis or arthroscopic epiosseous anchor tenodesis of the LHB tendon. The overall trial flow and timeline for data collection is outlined in Fig. 1.

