### Sample size calculation 

The primary objective of this study is to show the non-inferiority of loop tenodesis in comparison with arthroscopic anchor tenodesis with respect to the primary clinical outcome LHB score (scale range 0–100). The clinical non-inferiority margin was set at 5 points on the LHB score, which was based on statistical considerations and clinical judgment. Moreover, an expert panel of German-speaking shoulder surgeons was consulted on the study design and the choice of non-inferiority margin. The panel defined a non-inferiority margin of 5 points, taking into account the differences in LHB scores between the established procedures and the minimal clinically important differences in other related scores. For loop tenodesis to be considered standard of care and to show non-inferiority to implant-based tenodesis techniques, it has to outperform the technically easier procedure of biceps tenotomy. According to Kerschbaum et al. [26, 34], the mean LHB score of patients treated with biceps tenotomy is at least 5 points lower than that of patients treated with arthroscopic epiosseous suprapectoral anchor tenodesis. Setting the non-inferiority margin at 5 points can also be considered a benchmark for outperforming biceps tenotomy as a historical control, as suggested by studies by Kerschbaum et al. [26, 34]. Moreover, according to the literature [17, 25–28], we expect a mean LHB score of 85 with a standard deviation of 10 for both treatment groups at 12 months. The non-inferiority margin of 5 points is half of the expected standard deviation, which is widely accepted as the minimal clinically relevant difference of PROs [35]. To show non-inferiority with a non-inferiority margin of 5 points and a standard deviation of 10 points with a power of 90% at a one-sided 2.5% level of significance, a total of *n* = 172 patients are required for statistical analyses. Assuming an early drop-out rate of 10% (change of indication during arthroscopy and thus no need for surgery or no information on the clinical outcome (drop-out before week 6)), a total of *n* = 192 patients (96 per group) need to be randomized. Sample size was calculated by using SAS 9.4 and the procedure proc power.

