### Recruitment 

Different measures were taken to minimize recruitment challenges and to improve adherence to interventions:The selected inclusion and exclusion criteria are not overly restrictive and therefore allow the recruitment of the majority of patients with the tendon pathologies of interest at the enrolling centers.There are no competing trials at the enrolling centers, so that all eligible patients can be enrolled in this trail without confounding factors. Since there is no seasonal fluctuation of the incidence of LHB pathologies, constant recruitment throughout the entire recruitment period is possible.To reduce the complexity of the protocol, we chose a simple two-arm, parallel group design, omitting a third control group treated with simple tenotomy. Within the control group, a single tenodesis technique was clearly defined as the appropriate comparator.

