### Stopping rules

For patients: As guaranteed prior to study inclusion, the individual patient will be excluded from study participation if the patient withdraws his or her informed consent. Other stopping rules for patients are not applicable due to the single-day character of the trial intervention.For participating centers: Recruitment and protocol-compliant implementation of the follow-up examinations will be monitored by the DSMB throughout the entire trial period. If recruitment at the 50% landmark is less than 20% of the total target number of patients, the enrolling center will have to be excluded from participating in the trial.For the entire trial: If recruitment in more than one center is not possible, the Trial Steering Committee will be consulted to determine whether continuation of the trial is still realistic. If the incidence of adverse events of special interest with the trial intervention is significantly higher than that in the control group (> 50% more complications), continuation of the trial must be discussed with the DSMB and the Trial Steering Committee.

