Moreover, the prospective cohort study on the short-term outcome after loop tenodesis is a good indication that the targeted recruitment numbers are achievable. In the pilot study on mid-term outcomes after loop tenodesis, which was conducted as a single-center study in one of the recruiting institutes (Sporthopaedicum Regensburg), the same inclusion and exclusion criteria were applied. It was possible to enroll 55 patients within 7 months [17]. If the number of patients included in the pilot study is extrapolated to the recruitment period of 12 months as planned in the current RCT, the single reference center alone will be able to enroll 94 patients.

The study will provide high-evidence data for a new technique in the field of surgical treatment of the long biceps that is expected to provide the following benefits: non-inferior biceps function and cosmesis compared to current standard-of-care treatment and low complication rates.

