## Trial status

This is the first version of this protocol (August 2024). Recruitment of participants will start in December 2024 and is expected to conclude in November 2025. All patients will be followed up for 24 months. The final results are expected to be available after in December 2027 and disseminated via peer review publication and conference presentations.

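### As worded, the half-time recruitment threshold would exclude at least three of the five centers from a trial that is exactly on plan

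*Protocol article*

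**What the plan says.** The Stopping rules section has separate rules for patients, for participating centers and for the entire trial. The rule for centers sets the condition "If recruitment at the 50% landmark is less than 20% of the total target number of patients" and the consequence "the enrolling center will have to be excluded from participating in the trial". The wording of the consequence leaves no discretion.

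The figures needed to apply it stand elsewhere in the article:
- Trial flow gives the target as "One hundred ninety-two patients", 96 per group. The Sample size calculation section gives the same total.
- Study setting says "The trial will be conducted at five German medical centers".
- Trial status says "Recruitment of participants will start in December 2024 and is expected to conclude in November 2025", a 12-month period, and the Recruitment section expects that "constant recruitment throughout the entire recruitment period is possible".
- The Discussion extrapolates a single-center pilot (55 patients in 7 months) and concludes that "the single reference center alone will be able to enroll 94 patients".

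The article prints no recruitment target for any center. It does not say whether the 50% landmark refers to time or to enrolment.

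**The concern.** The threshold is a fraction of a trial-wide number but is applied to one center at a time, and at the halfway point. One fifth of the total is also the average final share of a center in a five-center trial. The rule therefore appears to ask for a full average share when only half the patients are due.

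This matters because the rule triggers a mandatory action. Followed literally, it removes most centers halfway through a trial that is recruiting as planned. If it is set aside because it is evidently unworkable, exclusion becomes a case-by-case decision, which a predefined rule is meant to prevent.

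**Working it through.** **The base figure.** The Sample size calculation section uses a margin of 5 points, an SD of 10, no true difference, and is set up "with a power of 90% at a one-sided 2.5% level of significance". The exact noncentral t calculation gives power 0.8999 with 85 per arm and 0.9032 with 86 per arm, so 2 × 86 = 172. With 10% drop-out, 172/0.9 = 191.1, rounded up to the even number 192. The plan's 172 and 192 both reproduce, so the base is sound.

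**The threshold as written.** 0.20 × 192 = 38.4, so a center escapes exclusion only with 39 or more patients.

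**Enrolment at the landmark.** With constant accrual over 12 months, half of the time (month 6) and half of the enrolment coincide on plan, at 192/2 = 96 patients.

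**How many centers can pass, under any split.** For k centers to pass, at least 39k patients must be enrolled:

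| Centers passing | Patients needed at the landmark |
|---|---|
| 2 | 78 |
| 3 | 117 (61% of 192) |
| 5 | 195 (more than the whole trial) |

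With 96 enrolled, 96/39 = 2.46, so at most two centers pass and at least three fail. This needs no assumption about how patients are spread over centers.

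**Equal shares (an assumption).** A center's full share is 192/5 = 38.4 and its on-plan count at half-time is 19.2, half of the threshold. All five fail.

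**The pilot rate in the Discussion.** The reference center would have 55/7 × 6 = 47.1 patients at month 6 and would pass. The other four would share 96 − 47.1 = 48.9. At most one of them could reach 39, so again at least three fail.

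**The analyzable number as base.** 0.20 × 172 = 34.4, so 35 patients are needed. Half of 172 is 86, and 86/35 = 2.46. Again at most two centers pass.

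**20% of the center's own target.** Under equal shares, 0.20 × 38.4 = 7.7, so 8 patients are needed against 19.2 expected. An on-plan center falls short with probability P(X ≤ 7) = 0.05% for a binomial count with n = 96 and p = 0.2, or 0.13% for a Poisson count with mean 19.2. This version would flag only centers that are clearly failing.

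**The case against.** The strongest reply is that the sentence can be read in context as meaning the center's own target. It stands among the rules for participating centers, its consequence falls on one center, and the word total may only contrast the full target with the halfway count. The next rule, for the entire trial, goes to the Trial Steering Committee when recruitment is impossible in more than one center. That suggests the authors regarded losing several centers as exceptional. Study setting also mentions predefined recruitment milestones, so center-level targets may well exist outside this condensed article.

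Much of this stands. The own-target reading is probably what was meant, and the article need not print the center targets. But the base is stated, it is the total number of patients, and the only such number given is 192. No other section supplies a different base, and a target held elsewhere would not change the words of the rule.

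It might also be said that the rule tests the recruitment of the whole trial. That does not fit, because the consequence is for a center and the entire trial has its own rule.

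Three stronger inferences are tempting but not supported:
- That every on-plan center must fail. This needs equal shares, which the article does not state and which its pilot extrapolation speaks against.
- That only the center of the pilot study would survive. This needs an assumed even split of the remaining patients over the other four centers.
- That the multi-center design would be lost. The DSMB monitors recruitment and would see an unworkable exclusion before it took effect. The rule for the entire trial concerns recruitment being impossible, and the text does not tie it to this threshold.

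**Conclusion.** The point holds for the rule as worded. With 192 as the base, at least three of five centers would have to be excluded in a trial exactly on plan. This rests on two things only: the literal base of the 20%, and 96 patients enrolled at the landmark, which follows from the planned constant accrual whichever way the landmark is defined. Failure of all five is the equal-shares case and should be presented as such.

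This is an error in an administrative decision rule. A reader might infer that it weakens the trial's statistical basis. It does not: the sample size reproduces, and the margin, the significance level, the estimands and the primary analysis are untouched. It should still be corrected, because the rule is mandatory and gives the wrong result if followed.

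**What to change.** In the Stopping rules section, under the rule for participating centers, replace the trial-wide total as the base of the 20% with the center's own recruitment target. In the same sentence, state whether the 50% landmark means half of the recruitment period or half of total enrolment. Either definition can work once the base is right.

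The individual center targets may remain in the full protocol or the monitoring plan, with a reference to them. The cost is one sentence, with no additional patients, visits or analyses.

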### Adverse event reporting and harms 

The occurrence of surgery-related adverse events of special interest (see Table 2) will be collected by each treating center throughout the follow-up period and recorded centrally at the Center for Clinical Studies (ZKS) of the University Hospital Regensburg. The safety assessments will be summarized by the statistician, and safety reports will be forwarded to the DSMB. In case of the occurrence of serious incidents, the enrolling center notifies the Federal Institute for Drugs and Medical Devices (BfARM).

**Table 2 Tab2:** Adverse events of special interest that will be monitored both intraoperatively (left) and postoperatively at each follow-up examination (right)

Intraoperative events	Postoperative events
Implant breakage/pullout	Displacement (Anchor migration/pullout, any change of the position of the tendon anchorage compared with previously documented position)
Implant malposition	Fracture of humeral head
Suture knot slippage/breakage	Bone cyst/osteolysis
Tendon slippage into the groove	Surgical site infection (superficial/deep)
Fracture	

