**Methods:**

A national multi-center, two-arm, parallel-group, randomized, controlled, non-inferiority trial will be conducted. Patients are eligible for trial participation if they are at least 18 years of age and present to one of the five enrolling centers with LHB tendon-associated complaints and MRI-confirmed LHB tendinopathy, instability due to SLAP or pulley lesions, or partial rupture. Patients with current or previous shoulder injury that would interfere with post-treatment rehabilitation or study assessment will be excluded from study participation. Participating patients will be randomized 1:1 to receive either LT or AAT and will be followed up for 24 months after surgery. The primary endpoint will be the functional and cosmetic outcome as assessed by the biceps-specific LHB score at 12 months after surgery. Secondary outcomes include assessment of surgery-related complications, overall shoulder and arm function, and structural outcome as evaluated by ultrasound and an additional MRI scan at the final study visit.

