## Introduction

### Background and rationale 

In the adult patient population, shoulder pain is commonly associated with pathologies of the long head of biceps (LHB) tendon [1]. While shoulder arthroscopy is the fourth most common procedure performed by orthopedic surgeons in the United States [2], up to 75% of these surgical procedures are associated with concomitant pathologies of the LHB tendon [3], which should be treated concomitantly to avoid revision surgery [4]. Besides, the number of arthroscopic LHB tenodesis procedures has steadily increased over the past decade as the field of indications has widened [5].

The benefits of tenodesis versus tenotomy for the treatment of the long head of the biceps tendon have been investigated in the past. A systematic review and meta-analysis that analyzed only RCTs and prospective cohort studies showed a threefold increased risk of Popeye deformity after arthroscopic tenotomy versus tenodesis [6]. Moreover, worse functional outcomes and a higher risk of cramping pain were observed after tenotomy [6]. The functional advantages and decreased rates of Popeye deformity after tenodesis compared to tenotomy have been confirmed in several meta-analyses [7, 8], but these analyses only included studies in which LHB pathologies were treated concomitantly with rotator cuff repair, which is a much more common setting than single treatment of the LHB tendon. Therefore, tenodesis is currently considered the gold standard for treating LHB tendon disorders. However, there are numerous tenodesis techniques that differ in the way the LHB tendon is reattached to bone or soft tissue and the location of reattachment. When comparing arthroscopic suprapectoral tenodesis procedures to open subpectoral techniques, systematic reviews and meta-analyses have reported a higher complication rate for open subpectoral tenodesis [9], although both treatments showed no significant difference in functional outcomes [9, 10]. Additionally, implant-associated complications have been reported regardless of the fixation location, including implant failure [11], increased rates of wound and implant infection [12, 13], and implant irritation [14]. These complications have contributed to a higher revision rate for implant-based LHB tenodesis compared to soft-tissue tenodesis [12].

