#### Secondary outcome measures

*Assessment of safety:* Another part of the hypothesis of the trial is that implant-free loop tenodesis is associated with fewer implant-related complications. A core set of adverse events of special interest has been set up for this study (see Table 2).

While intraoperative complications will be assessed during the performance of the randomized procedure, postoperative adverse events of special interest will be specifically queried at each follow-up visit. Such events will be graded according to the modified Clavien-Dindo classification for orthopedic surgery [31], depending on the need for outpatient or surgical/inpatient treatment. Since the overall complication rate is expected to be low, as seen in previous trials [9, 12], differences in the complication rates were not considered a primary endpoint and were thus not included in the sample size calculation.

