
Thus, the two techniques investigated in this trial differ in the way in which the LHB tendon is attached to the humeral bone (implant-based vs. implant-free) and is secured against slippage through the bicipital groove. By participating in the current trial, patients receive blinded treatment for LHB tendon pathologies. Although the experimental treatment group will be treated with a new surgical technique with little data available, we expect a high willingness to participate in the study because the details of the tenodesis technique usually play a subordinate role in patient perception and both the control intervention and the experimental intervention are already routinely performed surgical techniques in daily practice. Nevertheless, the recruitment plan requires patients to be enrolled regardless of concomitant pathologies and concomitant arthroscopic procedures. This is unavoidable because isolated pathology of the LHB tendon without accompanying shoulder pathologies accounts for only 5% of cases and is, therefore, a rarity in everyday clinical practice [44]. The sole inclusion of patients with isolated pathologies of the long biceps tendon would therefore not only question the feasibility of the recruitment target based on the sample size calculation, but would also not represent the reality of clinical practice. To overcome the limitation of heterogeneity of the study population and selection bias of the results, the biceps-specific LHB score was chosen as a primary outcome parameter for this trial. The score was introduced in 2011 [25] in order to provide a useful tool for the highly specific evaluation of the LHB tendon after surgery, because the most established shoulder scores only incompletely cover LHB tendon disorders and mainly depend on the results of concomitant procedures. The LHB score has proven to be a valuable tool for evaluating outcome after LHB tenotomy and tenodesis procedures in previous studies [17, 25–30].

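### Structured safety collection, grading and the safety triggers cover nine listed events with no line for any other complication, so a low-complication statement would hold only for those events

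*Protocol article*

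**What the plan says.** The abstract (Methods) sets a broad safety outcome: "Secondary outcomes include assessment of surgery-related complications". The Objectives section treats safety as a matter of primary concern. Secondary outcome measures adds the hypothesis that the loop technique causes fewer implant-related complications.

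The operational text is narrower. Secondary outcome measures states: "A core set of adverse events of special interest has been set up for this study (see Table 2". On elicitation it says that "postoperative adverse events of special interest will be specifically queried at each follow-up visit", and it applies the modified Clavien-Dindo grade to those events. Adverse event reporting and harms repeats the scope: "The occurrence of surgery-related adverse events of special interest (see Table 2) will be collected by each treating center throughout the follow-up period". The caption of Table 2 reads "Adverse events of special interest that will be monitored both intraoperatively (left) and postoperatively at each follow-up examination (right".

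The Discussion concedes that "the experimental treatment group will be treated with a new surgical technique with little data available". It also lists, as an expected benefit, "non-inferior biceps function and cosmesis compared to current standard-of-care treatment and low complication rates".

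**The concern.** A predefined list finds the harms its authors already expect. For a technique with a short record, the complications of most interest may be those nobody listed. If the form has no place for them and no open question prompts for them, the complication count in each arm can be too low, and the comparison of arms can be incomplete in either direction. An unlisted problem with the loop would be missed, and so would implant irritation in the anchor arm.

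Two things are at stake. One is what the DSMB sees while the trial runs. The other is what the final report may claim: a low complication rate would partly reflect what the form asked about.

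**Working it through.** The article gives no complication rate, and safety was left out of the sample size calculation, so there is no planned figure to reproduce. The check is a count, a tracing of routes and an illustration of scale.

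**1. Lines in Table 2.**
- Intraoperative: implant breakage/pullout; implant malposition; suture knot slippage/breakage; tendon slippage into the groove; fracture. That is 5.
- Postoperative: displacement; fracture of the humeral head; bone cyst/osteolysis; surgical site infection. That is 4.
- Total 5 + 4 = 9. There is no line for other events. Two of the nine (implant breakage/pullout and implant malposition) can arise only where an implant is used, as can the anchor part of displacement.

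**2. Which events each safety step refers to.**
- Schedule (Table 1): the only adverse event row is for adverse events of special interest.
- Querying and grading (Secondary outcome measures): the same events; no open question is mentioned.
- Collection (Adverse event reporting and harms): the same events, by reference to Table 2.
- Full source data verification (the section on the data monitoring committee): among adverse events, only these are named.
- DSMB advice on continuing the trial (the section on the coordinating center and DSMB): accumulation of these events.
- Whole-trial safety trigger (Stopping rules): incidence of these events in the loop arm against control.

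All of these steps name the same list. The article therefore fixes the scope; it does not merely omit a detail.

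**3. The Background's implant complications against Table 2.** Background and rationale names implant failure, and then "increased rates of wound and implant infection [12, 13], and implant irritation [14".
- Implant failure: covered by implant breakage/pullout and by displacement.
- Wound and implant infection: covered by surgical site infection.
- Implant irritation: no line.

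One of the three kinds of complication behind the hypothesis of fewer implant-related complications is not collected as such.

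**4. Other routes.**
- Reoperations, additional operations and further biceps tendon injuries are intercurrent events in Statistical methods, so they must be recorded. They are not described there as graded safety data.
- Pain, cramps, tenderness, Popeye deformity and flexion strength enter the LHB score, but not as counted complications.
- Serious incidents are notified to the federal authority; the DSMB is not named in that sentence.

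What remains is a complication that is unlisted, needs no reoperation, is not a biceps injury and is not a serious incident. A nerve lesion, haematoma or stiffness managed conservatively is an example. No stated route takes it into the graded safety data.

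**5. Scale.** Input from the article: 192 / 2 = 96 patients per arm. Assumed, because the article gives none: a rate p of unlisted complications of 1%, 3% or 5%. Expected number = 96 × p; chance of at least one = 1 − (1 − p)^96.
- p = 1%: 0.96 events; 62%.
- p = 3%: 2.88 events; 95%.
- p = 5%: 4.80 events; 99%.

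For comparison, if a given complication were asked about and none occurred in 96 patients, the one-sided 95% upper limit for its rate would be 1 − 0.05^(1/96) = 3.1%. A zero from a form that never asked gives no such limit.

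**The case against.** A reader might infer more: that unexpected harm is neither recorded nor sent to the DSMB, and that no low-complication conclusion can be supported. The article does not support that.

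- The list is called a core set and is nowhere said to be exhaustive. The full protocol and the eCRF are not shown and may contain a field for other events.
- The article says that safety reports go to the DSMB without limiting their content, and does not say that serious incidents bypass it.
- Surgical complications surface as intercurrent events. Persistent pain, stiffness or weakness would be expected to affect the LHB, Constant, ASES or DASH scores or the strength measurements, and ultrasound is done at each follow-up visit.
- A focused list fits the narrow hypothesis about implant-related complications. Only about 5% of cases are isolated biceps pathology (Discussion), so an open line would also collect events from concomitant procedures.
- Low complication rates are an expected benefit in the Discussion; the planned safety analysis is descriptive.
- Leaving out irritation undercounts the anchor arm, which works against the trial's own hypothesis.

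These points stand as limits on the wording. They do not remove the concern. A change in a score is not a graded complication, and an intercurrent event is recorded for the estimand. If the full protocol does collect other complications, the article's harms section misdescribes the scope and needs the same correction. Even on the narrow hypothesis, the list lacks a complication that the Background itself names.

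**Conclusion.** The point holds in this form: as the article describes it, structured collection, querying, grading and both safety triggers are limited to nine listed events, with no line for any other complication and none for implant irritation. A general statement about low complication rates would be valid only for the listed events.

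The size is unknown. About 1 to 5 unlisted events per 96 patients follows only from an assumed 1% to 5%. A reader might also infer that unlisted events would match the listed ones in number. The article gives no basis for that: it expects the overall complication rate to be low and gives no rate for the listed events. The net direction of any error in the comparison of arms cannot be determined either. The primary endpoint, sample size and randomization are unaffected. The verdict rests on the article's text; the eCRF could show that the practical gap is smaller.

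**What to change.** - Add to each column of Table 2 a line for any other complication of the operated shoulder or arm, with free text, date and modified Clavien-Dindo grade. Prompt for it with an open question at each visit.
- Add implant irritation as a named postoperative line.
- Include both in the safety reports to the DSMB, and say so in Adverse event reporting and harms.
- Report by arm, separately, the listed events and all complications. Mark events attributed to a concomitant procedure.
- If the eCRF already has such a field, state this in the article. If the sponsor prefers to keep the list as it is, limit the safety conclusion to the events in Table 2.

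The cost is a few fields on an existing eCRF page, an additional row or two in the safety tables and some coding work. More minor events will be reported, including some from concomitant procedures; the marking deals with those.
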